##### Quantitative Data Collection and Analysis

The initial questionnaire for objective 2 will gather fundamental sociodemographic information (eg, year of birth, preferred language, gender, and ethnic group identity) and digital technology use (Multimedia Appendix 8).

Descriptive statistics will be used to depict the sociodemographic characteristics and digital technology use of the participants. Continuous variables will be reported using measures such as minimum, maximum, mean, and SD. In the case of ordinal and nominal qualitative variables, we will report both counts and proportions.

Global usability will be collected using 2 validated scales: the *shorter version of the Usability Metric for User Experience* (*UMUX-Lite*) [50] and the *Acceptability E-scale* (*AES*) [51] (Multimedia Appendix 8).

Usability is defined in part as “the extent to which a product can be used to be effective, efficient, and provide users’ satisfaction within its defined goal” [52]. The UMUX-Lite is a 2-item questionnaire answered on a 7-point Likert scale that is deemed appropriate for use in the evaluation of health technology [53]. The items ask whether the chatbot meets user needs and about perceived ease of use.

Acceptability is related to how agreeable, palatable, or satisfactory an intervention is perceived to be by stakeholders and is also considered part of global usability [14]. The AES contains 6 items rated on different 5-point Likert scales. It is a validated measure of the acceptability and usability of computer-based interventions for health care populations. Items evaluate, for example, how easy and enjoyable the innovation is to use, how helpful it is, and whether the amount of time to engage with it is acceptable.

As continuous outcomes, both usability and acceptability will be summarized using the minimum, maximum, mean, and SD. The sample mean of each global usability outcome will be compared with its recommended usability thresholds—68/100 for the UMUX-Lite score and 24/30 for the AES score—using a Student *t* test. It will test the null hypothesis that the average UMUX-Lite score is ≤68 and that the average AES score is ≤24. A significance level of 5% will be adopted.

Four central subconstructs of the Technology Acceptance Model (TAM) framework will also be assessed as secondary end points via validated instruments to complement the data: (1) perceived ease of use, (2) perceived usefulness, (3) attitude toward use, and (4) behavioral intention to use the chatbots.

Perceived ease of use will be measured using the Single Ease Question [54], which is answered on a 7-point Likert scale.

Drawing on instruments by Chau and Hu [55] and Davis [56], perceived usefulness will be measured on a 7-point Likert scale with 4 items slightly adapted for relevance to chatbots. The final score will be the average of these items.

Attitude toward using chatbots will be measured using the net promoter score (NPS) [57], which is used as a measure of user satisfaction. A single question will be asked on an 11-point Likert scale. To calculate the NPS, 3 groups are created: promoters (score of 9-10), passives (score of 7-8), and detractors (score of 0-6). Subtracting the percentage of detractors from that of promoters provides the NPS (range −100 to 100). Positive scores, and especially those of >50%, are judged positively.

Finally, behavioral intention to use the chatbots will be assessed using a validated 2-item questionnaire [58] rated on a 7-point Likert scale averaged to produce a final score.

Predicted positive associations between subconstructs within the TAM framework will be evaluated using simple linear regressions considering the slope coefficient. Their significance will be tested using a Student *t* test.

All statistical analyses will be conducted using the R software (R Foundation for Statistical Computing) [59].

##### Qualitative Data Collection and Analysis

Participants’ experiences with MARVIN will be explored through a semistructured focus group on the main constructs of the TAM framework (ie, usefulness, ease of use, attitude, and behavioral intention to use), the analysis of which will help further explain the quantitative analysis. A focus group interview guide can be found in Multimedia Appendix 8.

A composite coding matrix based on the TAM and the nonadoption, abandonment, scale-up, spread, and sustainability (NASSS) framework will be favored for deductive content analysis [60]. The NASSS framework [61] was developed to support the implementation and scale-up of technological innovations in health care. It includes seven relevant domains: (1) the illness or condition, (2) the technology, (3) the value proposition, (4) the adopter system, (5) the organization, (6) the wider context, and (7) embedding and adaptation over time. Given that 5 to 7 are more focused on scaling up implementation, objective 2 will likely focus on the first 4 subdomains for analysis to illustrate associated barriers and facilitators of the early phases of implementation. All facilitators and barriers identified will be then subsequently matched to the subconstructs of the TAM, when possible, to understand their impact on global usability.

The content analysis involves 3 phases. In phase 1, preparation, the analyst will attempt to understand the entire data set through immersion in the data. In phase 2, organization, a composite coding matrix will be devised using the NASSS domains and the TAM subconstructs. The data will be coded and categorized using NVivo R1. Finally, in phase 3, reporting, the descriptive content of the categorization will be presented, addressing trustworthiness.

The saved transcripts of users’ conversations with the chatbots may also be submitted for content analysis to describe and better understand the nature of chatbot-participant interactions, such as conversation topic trends.

#### Objective 3: Implementation Assessment

##### Overview

For this objective, we will further assess the implementation outcomes of the MARVIN chatbots after they are deployed to the general population via Messenger. During this stage, the chatbots will be regularly updated to introduce new features or content, and their impact on implementation will be assessed. If the outcomes are negative, the corresponding version of the chatbot will be submitted for continuous improvement and evaluation.

We anticipate that the participation period will be 12 months and could be adjusted according to the health care context. Participants will receive a link to the same sociodemographic questionnaire as before (ie, via REDCap [Research Electronic Data Capture; Vanderbilt University] or Google Forms) directly through the chatbot at entry into the study (Multimedia Appendix 8). They will then be able to send messages to MARVIN whenever they wish. If the chatbot does not receive a message from the participant within a month of its most recent conversation with them, it will proactively ask the participant the following: “It’s been a month since our last conversation. How have you been?” The participant will be able to turn off this inquiry if they so wish.

Every 2 months, participants will receive a link to a questionnaire on implementation outcomes (Appendix 7). The chatbot will also ask 3 open-ended questions to collect information on the participant’s overall experience and suggestions for continuous improvement of the chatbot.

##### Quantitative Data Collection and Analysis

The implementation outcome questionnaire will assess usability, acceptability, and appropriateness using validated instruments. Fidelity and adoption will be summarized using descriptive statistics on chatbot use metadata.

Usability and acceptability will be measured for objective 3 (implementation) as they will be for objective 2 (usability) using the UMUX-Lite and AES questionnaires as both measures are dynamic and vary with experience. Thus, usability and acceptability ratings may be different for each stage of implementation [14,62].

Appropriateness relates to the relevance or compatibility of the innovation to address a particular issue or problem [14]. The compatibility of an IT innovation is the extent to which it is considered consistent with users’ values, needs, and past experiences [63]. The *Compatibility Subscale* is a validated tool that contains 3 items rated on a 7-point Likert scale (range 1-7) to assess how an IT innovation “fits” with the user’s work style [64]. An adapted version will be administered to health care professional participants. A minimum average score of 5.5 is set as the threshold for adequate compatibility. For patient participants, the *Intervention Appropriateness Measure* will be used [65]. It contains 4 items scored on a 5-point scale to assess an innovation’s suitability for a user. A mean score of at least 4 will indicate the appropriateness of the chatbot intervention for the patient population.

Fidelity is the degree to which the intervention is implemented as intended [14]. On the basis of the fidelity measures of digital health intervention implementation identified by Coorey et al [66], we will analyze the following metadata to comprehensively assess the chatbot fidelity: (1) intervention fidelity (the proportion of participants who continue to use the chatbot after a 1-month period), (2) frequency and duration (the monthly frequency with which participants use the chatbot and the average total duration of using the chatbot), (3) messages delivered (the total number of messages that participants interacted with in the chatbot over the course of the study period as well as the average number per participant), and (4) range of messages received (the frequency distribution of different conversational topics triggered by all participants).

Adoption, or uptake, is “the intention, initial decision, or action to try or employ an innovation or evidence-based practice” [14]. It will be measured using the proportion of monthly new users enrolled to all users in the study. The target will be 5% per month given that the median user growth rate for small-scale software services is 4.4% [67,68].

Statistically, a strategy similar to that of objective 2 will be adopted to describe the data. For usability, acceptability, and appropriateness, a Student *t* test will be used to test the null hypothesis that the average score is inferior or equal to the predetermined thresholds.

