**Methods:**

The MARVIN chatbots study has an adaptive platform trial design consisting of multiple parallel individual chatbot substudies with four common objectives: (1) co-construct a tailored AI chatbot for a specific health care setting, (2) assess its usability with a small sample of participants, (3) measure implementation outcomes (usability, acceptability, appropriateness, adoption, and fidelity) within a large sample, and (4) evaluate the impact of patient and stakeholder partnerships on chatbot development. For objective 1, a needs assessment will be conducted within the setting, involving four 2-hour focus groups with 5 participants each. Then, a co-construction design committee will be formed with patient partners, health care professionals, and researchers who will participate in 6 workshops for chatbot development, testing, and improvement. For objective 2, a total of 30 participants will interact with the prototype for 3 weeks and assess its usability through a survey and 3 focus groups. Positive usability outcomes will lead to the initiation of objective 3, whereby the public will be able to access the chatbot for a 12-month real-world implementation study using web-based questionnaires to measure usability, acceptability, and appropriateness for 150 participants and meta-use data to inform adoption and fidelity. After each objective, for objective 4, focus groups will be conducted with the design committee to better understand their perspectives on the engagement process.

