For objective 3 (implementation), an optimized version of the chatbot will be accessible from the web around the clock, 7 days a week, for translational research. As currently the MARVIN chatbots will be only released in Canada, recruitment will be exclusive to the Canadian population, and participants will engage in an electronic consent process through the MARVIN chatbots. Before using the chatbot, individuals will be required to review and accept MARVIN’s privacy policy (Multimedia Appendix 5). Subsequently, they will be asked to review an electronic version of the information and consent form and then answer the following verification questions for eligibility criteria 1 to 3 via the chatbot: (1) *Are you at least 18 years old?* (2) *Are you comfortable using English or French while communicating with the chatbot?* (3) *Do you agree to participate in the study as described above?* The remaining criteria (4 to 8) will be met once users connect to the chatbot. Should participants agree to participate, their responses will be securely recorded in a separate encrypted database on the MARVIN cloud servers and synchronized to the electronic enrollment log. If users opt not to participate, no records will be kept. As a Facebook account will be a prerequisite for using the chatbot, no further measures will be taken to detect or prevent the possibility of multiple identities. The target sample size of 30 to 150 participants was obtained based on the usability, acceptability, and appropriateness outcomes, which are considered key outcomes for this objective. The analysis involves a 1-sided Student *t* test (1-tailed) evaluating whether the corresponding average attains a predetermined threshold. A power analysis for a 1-sample *t* test is then performed, with 80% power and a 5% significance level. Within the targeted sample size (30≤n≤150), small to moderate standardized effect sizes (0.2≤Cohen *d*≤0.5) are detectable in the total sample with the aforementioned statistical power.

Regarding objective 4 (partnership evaluation), upon completion of each objective, an email invitation will be sent to organize focus groups with stakeholders involved in the chatbot co-construction design committee.

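### The adoption ratio (monthly new users over all users, target 5% per month) does not change with the size of uptake, so meeting or missing the target cannot tell good uptake from poor

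*Protocol article*

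**What the plan says.** Adoption is one of the five implementation outcomes listed for Objective 3 under Aim and Objectives. The Objective 3 section on quantitative data collection and analysis defines it as "the intention, initial decision, or action to try or employ an innovation or evidence-based practice". The same section gives the measure: "It will be measured using the proportion of monthly new users enrolled to all users in the study". The criterion follows: "The target will be 5% per month given that the median user growth rate for small-scale software services is 4.4" percent.

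Three other statements bear on the point:

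- The analysis is descriptive: "Fidelity and adoption will be summarized using descriptive statistics on chatbot use metadata".
- The Objective 3 overview attaches a consequence to poor results: "If the outcomes are negative, the corresponding version of the chatbot will be submitted for continuous improvement and evaluation".
- Under Recruitment and Sample Size Justification, people who decline leave no trace: "If users opt not to participate, no records will be kept".

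The article does not say whether the denominator is the running total or the final total, or whether 5% must hold in every month or on average.

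**The concern.** Numerator and denominator both count people who have already enrolled. The ratio therefore describes how enrolment is spread over time and says nothing about how many people took the chatbot up, or what share of those who met it did so. A target on such a ratio can be met with negligible uptake and missed with good uptake.

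The 5% figure is the only criterion the article states for adoption, and negative outcomes send a version back for improvement. Because this is a master protocol, the same measure passes to every substudy that reaches Objective 3. A chatbot that hardly anyone uses could be reported as having met its adoption target.

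**Working it through.** **Inputs.** The ratio and the 5% target come from the Objective 3 quantitative section. The 12 months come from the abstract ("the public will be able to access the chatbot for a 12-month real-world implementation study") and the Objective 3 overview ("We anticipate that the participation period will be 12 months and could be adjusted according to the health care context"). The total of 150 is the abstract's figure; the recruitment section gives 30 to 150. The article states no launch size or monthly enrolment, so the patterns below are assumptions chosen to span a range. The 5% is a chosen benchmark, so there is no plan figure to reproduce.

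**1. Steady enrolment of m users a month, cumulative denominator.** The ratio in month t is m / (m × t) = 1/t, and m cancels.

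| Month | 1 | 2 | 3 | 6 | 12 | 20 | 21 |
|---|---|---|---|---|---|---|---|
| Ratio | 100% | 50% | 33.3% | 16.7% | 8.3% | 5.0% | 4.8% |

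The series is the same for m = 1 (12 users in a year) and m = 12.5 (150 users). Both meet 5% in 12 of 12 months, and the first miss is month 21.

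**2. Other denominators, steady enrolment.** With the final total, every month is 1/12 = 8.3%. With users before month t, the ratio is 1/(t − 1), or 9.1% in month 12. The target is met on each.

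**3. Averaging over 12 months.** With the final total as denominator, the 12 monthly values sum to 100%, so the mean is 100/12 = 8.3% for any pattern. With the cumulative denominator, month 1 alone contributes 100%, so the mean is at least 100/12 = 8.3% whenever anyone enrols in month 1. Neither average can fall below 5%.

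**4. Front-loaded launch: L users in month 1, then m a month, cumulative denominator, judged month by month.** The ratio in month t ≥ 2 is m / (L + (t − 1)m).

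- L = 100 and 50 more over months 2–12, so m = 50/11 = 4.55. Month 2: 4.55/104.55 = 4.3%. Month 12: 4.55/150 = 3.0%. The target is missed in all 11 later months, with 150 users reached.
- L = 100, m = 10: only month 12 is missed (10/210 = 4.8%).
- L = 100, m = 12: no month is missed (month 12: 12/232 = 5.2%).

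Thresholds: month 12 passes if m ≥ 0.05(L + 11m), that is 0.45m ≥ 0.05L, so m/L ≥ 1/9 = 11.1%. Month 2 passes if m/L ≥ 0.05/0.95 = 5.3%. Below 5.3% all 11 later months are missed; between 5.3% and 11.1% only some are.

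**5. Scale.** 1000 users in month 1 then 40 a month (1440 in total) gives the same percentages as 100 then 4 a month (144 in total): 3.8% in month 2 falling to 2.8% in month 12.

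**The case against.** The strongest reply concerns consequence. Adoption carries no test, and the sample size rests on usability, acceptability and appropriateness, which the recruitment section names as the key outcomes. The decision to continue to Objective 3 rests on Objective 2. A negative outcome in Objective 3 only returns a version for improvement, at a stage when versions are regularly updated anyway. All of this stands, and it limits the severity. It does not repair the target.

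Four stronger readings are tempting, and the article does not support them:

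- *One user a month would make the substudy a success.* Twelve users falls short of the stated minimum of 30, so the shortfall would be visible elsewhere. Only the adoption target would be met.
- *The measure says nothing about uptake.* The numerator, people who enrol in a month, fits the quoted definition. The Objective 2 descriptive strategy, which Objective 3 follows, reports counts beside proportions for categorical variables, and an enrolment log is kept. Those counts would separate 12 users from 150.
- *A fast launch fails.* On the cumulative denominator this needs a month-by-month rule, which the text does not state, and later enrolment below about 11% of the launch month. A launch with strong continued enrolment passes, and so does the 12-month average of a front-loaded one.
- *The 4.4% benchmark is on the wrong scale.* The article does not define that growth rate. If it means new over prior users, 4.4% becomes 0.044/1.044 = 4.2% as a share, and a 5% share is 5.3% growth. The target exceeds the benchmark on either scale.

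It may also be said that subprotocols will settle the denominator and the averaging rule. They can, but none of the denominators examined makes the ratio depend on the level of uptake.

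**Conclusion.** The point holds for the ratio and its 5% target. The ratio is independent of the size of uptake on every denominator examined. Any steady enrolment meets 5% throughout the planned 12 months, and a 12-month average over the final total is fixed at 8.3%. On a month-by-month reading with a cumulative denominator, a substudy that reaches 150 users can miss the target in 11 of 12 months while one with 12 users never misses. Meeting or missing 5% therefore does not discriminate good from poor uptake.

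The severity is moderate: adoption is descriptive, no inference or sample size depends on it, and the raw counts would still inform. The conclusion assumes 12 monthly values. Steady enrolment would fall below 5% only from month 21, so the adjustable period matters only if it becomes much longer. The enrolment patterns are illustrations; the article forecasts none.

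**What to change.** 1. Remove 5% per month as a success criterion. If the ratio is kept, keep it as description and define its denominator.
2. Report monthly new and cumulative consented users against an enrolment figure that each subprotocol states in advance. The article states no planned rate. For orientation, its 30 to 150 participants spread over 12 months would be 30/12 = 2.5 to 150/12 = 12.5 a month.
3. Optionally, add the proportion of people reaching the consent screen who enrol and send at least one message, using an anonymous aggregate counter. This brings in people who were reached but did not adopt. It still leaves out eligible people who were never reached.

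Items 1 and 2 cost only protocol wording, because the counts are already collected. Item 3 must be reconciled with the statement that no records are kept of people who decline, and it may need a research ethics board amendment. None of the three needs extra participants.

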##### Qualitative Data Collection and Analysis

To better understand the implementation outcomes, participants will be invited to answer three open-ended questions: (1) What did you like most about using MARVIN? (2) What did you dislike about using MARVIN? (3) How would you improve MARVIN?

The content analysis of this material using the same coding matrix as in objective 2 will likely include the last 3 subdomains of the NASSS framework given the implementation stage at objective 3. This will help document and detail barriers to and facilitators of using the chatbots and their associated implementation outcomes as well as identify targets for continuous improvement.

As with objective 2 (usability), the saved transcripts of chatbot conversations may also be submitted for content analysis to characterize and better understand the nature of chatbot-participant interactions.

#### Objective 4: Evaluate the Impact of Different Stakeholder Partnerships

##### Overview

The reporting of patient and stakeholder engagement roles will follow the revised Guidance for Reporting Involvement of Patients and the Public [69].

##### Quantitative Data Collection and Analysis

Quantitative data on patient and stakeholder engagement activities, such as the number and length of actual workshops or focus groups conducted; the number of attendees; and the user requirements, design parameters, and improvement recommendations made by stakeholders during the workshops or focus groups, will be reported to illustrate the impact of patient and stakeholder engagement on the adaptation or development of the MARVIN chatbots.

